#### *Phase* 1 [Baseline ~ 1 month from the baseline (± 2 weeks)]

The goal of the exercise program during the first phase is to facilitate the recovery of shoulder ROM and strength in breast cancer patients post-operatively. Prescription of exercise is emphasized to improve shoulder recovery and maintain whole-body function. Therefore, exercise programs should include tailored calisthenics exercises based on the patients’ shoulder joint condition. During this phase, no structured aerobic exercise program will be provided to patients. The very low-intensity calisthenics exercise program consists of nine different exercises. Specific exercises include neck stretching, shoulder rotation stretching, shoulder retraction, a clasp with a small ball, pendulum exercise, pelvic tilt on the wall, back extension, calf raise, and seated leg extension on a chair. For each exercise, the participants will perform 1–5 sets of 3–5 repetitions or 3–5 s with an accepted form recommended by exercise specialists (Supplementary 1). The very low-to low-intensity calisthenics exercise program consists of 11 different exercises. The specific exercises include neck stretching, shoulder rotation stretching, shoulder retraction, a clasp with a small ball, pec-dec fly, pendulum exercise, child pose, back extension, pelvic tilt on the wall, calf raise, and seated with the leg extended on a chair. For each exercise, participants will perform 1–5 sets of 3–5 repetitions or 3–5 s with an accepted form recommended by exercise specialists (Supplementary 2). The low-intensity calisthenics exercise program consists of 11 exercises. The specific exercises include neck stretching, shoulder rotation stretching, shoulder retraction, a clasp with a small ball, pec-dec fly, pendulum exercise, child pose, back extension, pelvic tilt on the wall, calf raise, and seated leg extension on a chair. For each exercise, participants will perform 1–5 sets of five repetitions or 5 s with an accepted form recommended by exercise specialists (Supplementary 3).

#### *Phase* 2 [POD 1 month ~ 6 months from the baseline (± 1 month)]

The goal of the exercise program during this phase is to obtain full shoulder ROM and strength recovery and to maintain cardiopulmonary fitness and muscle mass. Tailored calisthenics and aerobic exercises will be implemented. During this period, participants will be encouraged to engage in at least 150 min of moderate-intensity exercise in conjunction with detailed daily calisthenics exercise weekly. The low-to moderate-intensity calisthenics exercise is composed of 11 different exercises with low to moderate difficulties. The specific exercises include neck stretching, shoulder rotation stretching, shoulder retraction, a clasp with a small ball, pec-dec fly, pendulum exercise, child pose, back extension, pelvic tilt on the wall, calf raise, and sitting with the leg extended on a chair. For each exercise, participants will perform 1–5 sets of five repetitions or 5–10 s with an accepted form recommended by exercise specialists (Supplementary 4). The moderate-intensity calisthenics exercise program consists of 10 different exercises. The specific exercises include the following: neck stretching, shoulder rotation stretching, cross-chest stretching, scapular retraction, bird dog, child pose, back extension, pelvic tilt on the wall, chest stretching, and chair squats. For each exercise, participants will perform 1–10 sets of five repetitions or 5–10 s with an accepted form recommended by exercise specialists (Supplementary 5). For participants whose shoulder ROM or strength have not fully recovered, tailored shoulder exercises will be included.

#### *Phase* 3 [6 months (± 1 month) ~ 12 months from the baseline (± 1 month)]

The goal of the exercise program during this phase is to improve cardiopulmonary fitness and increase muscle strength and mass. Tailored calisthenics and aerobic exercises will be implemented. During this period, participants will be encouraged to engage in at least 150 min of moderate-to high-intensity physical activities (at least 75 min of high-intensity physical activity will be recommended) in conjunction with detailed daily calisthenics exercise per week. The moderate-to-vigorous-intensity calisthenics exercise is composed of 11 different exercises. Specific exercises include neck stretching, modified chest stretching, cross-chest stretching, scapular retraction, chair squat, child pose, back extension, bird dog, pelvic tilt on the wall, chest stretching, and Y stretching. For each exercise, participants will perform 1–10 sets of five repetitions or 5–10 s with an accepted form recommended by exercise specialists (Supplementary 6). The vigorous-intensity calisthenics exercise program consisted of 12 exercises. The specific exercises include neck stretching, modified chest stretching, modified pec-dec fly, cross-chest stretching, bicycle crunch, bird dog, wall push-up, chest stretching, Y-stretching, and dynamic squat. For each exercise, participants will perform 1–10 sets of five repetitions or 5–10 s with an accepted form recommended by exercise specialists (Supplementary 7).

### Study outcome measures

#### Primary outcome measures

[The evaluation schedule: at baseline, 6 months from the baseline (± 1 month), and 12 months (± 1 month; Primary outcome)]. After an overnight fast (≥ 10 h) blood would be obtained from the participants, and separated serum samples will be immediately stored at − 80 °C until they are assayed. Fasting insulin levels will also be measured using chemiluminescent enzyme immunoassays (Roche, IN, USA).

### Secondary and ancillary Outcomes Measures

#### Shoulder ROM

[The evaluation schedule: at baseline, 1 month from the baselines (± 2 weeks), 6 months from the baseline (± 1 month), and 12 months (± 1 month)]. Shoulder passive ROM, including flexion, abduction, and extension, will be measured using a goniometer (goniometer bending iron 29-5900, Pakistan) and standardized assessments (Norkin, 2004). All measurements will be performed on both the affected and unaffected arms, and the mean values will be used.

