#### Exclusion criteria

This study will exclude [1] patients who were scheduled for bilateral breast surgery; [2] immediate breast reconstruction surgery; [5] mental impairment leading to inability to cooperate; [6] current pregnancy or plans to become pregnant within the 1 year; and [7] any other condition or intercurrent illness (as assessed by the investigator).

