#### Shoulder strength

[The evaluation schedule: at baseline, 1 month from the baselines (± 2 weeks), 6 months from the baseline (± 1 month), and 12 months (± 1 month)]. Shoulder strength will be measured using a handheld dynamometer (j-tech Medical Industries Inc., UT, USA) in pounds (lb). The strength of peak muscle force will be measured using maximal voluntary isometric contraction (MVIC) in flexion, abduction, and extension [37]. All muscular strength measurements will be performed twice with both the affected and unaffected arms, and the average values will be used for the analysis.

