#### Statistical analysis methods

All analyses will be performed using the SPSS version 26.0 software (IBM Corp., Armonk, NY, USA). A Chi-square test for categorical variables and an independent t-test for continuous variables will be used to test group differences at baseline. Two-way repeated-measures ANOVAs will be conducted to observe the effects of the intervention on fasting insulin levels, shoulder ROM and function, body composition, inflammatory markers, microbiome, QOL, and physical activity levels. Paired t-tests will be performed to examine the difference between outcome measurements and baseline values, while independent t-tests will be employed to examine group differences in variables at each time point. The Bonferroni correction method will be used to correct for multiple tests. Analysis of covariance (ANCOVA) will be applied to test the effect of an exercise intervention on body composition, PA, and complications, since these variables will be measured after adjusting for baseline values. First, from baseline to 1 month from the baseline will be calculated and then the differences between groups will be examined after adjusting for baseline values and surgical methods. The same methods will be used for 6 and 12 months.

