During Phase I (surgery to 1 month), the most prevalent comorbidity following breast cancer surgery is poor shoulder function, including a decrease in ROM and impaired strength [52]. One recent study showed that recovery of ROM differs by surgery type; however, shoulder strength was reduced regardless of the surgery type [28]. It was also reported that reduced shoulder strength in the unaffected arm suggests reduced shoulder strength in both the affected and unaffected arms due to lack of utilization [28]. A recent study found that shoulder ROM and strength recover to pre-surgery levels within 1 month after surgery if a proper exercise program is implemented [35]. Taken together, these studies suggest that exercises focused on the recovery of shoulder function should be emphasized during this phase.

During the chemotherapy period (phase 2), patients with breast cancer typically experience muscle mass loss [53], insomnia [54], cardiotoxicities [45], and fatigue [46]. Exercise intervention improves these parameters [55] and the recent American Society of Clinical Oncology guidelines clearly recommend oncology providers recommend aerobic and resistance exercises during active treatment with curative intent to mitigate the side effects of cancer treatment [51]. Furthermore, exercise intervention during chemotherapy may improve the chemotherapy completion rate [56] and reduce the hospitalization rate [57], although the effect of exercise on chemotherapy completion remains controversial [58]. Furthermore, during hormone therapy, more than 60% of patients experience joint and muscle pain [59], which can be improved through proper exercise [60]. Although exercise could be beneficial for breast cancer survivors during this period, shoulder dysfunction, fatigue, and low fitness levels could be barriers to exercise. Therefore, exercise programs during this period should be tailored to the patients’ physical condition with the aim of maintaining muscle mass and fitness.

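### As written, shoulder ROM is the mean of the operated and the unoperated arm, which halves in degrees any effect confined to the operated side; the strength rule is only ambiguous

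*Protocol article*

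**What the plan says.** The Shoulder ROM section describes passive flexion, abduction and extension measured by goniometer, and then gives the rule for forming the value: "All measurements will be performed on both the affected and unaffected arms, and the mean values will be used". It mentions no repeated readings.

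The Shoulder strength section has a similar sentence with one difference. The measurements are "performed twice with both the affected and unaffected arms, and the average values will be used for the analysis". Here there are two trials as well as two arms.

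Three other places bear on the reading:

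- The Exclusion criteria remove "patients who were scheduled for bilateral breast surgery", so every participant has one operated side.
- The goal of Phase 1 is "to facilitate the recovery of shoulder ROM and strength in breast cancer patients post-operatively".
- The Statistical analysis methods section says: "Two-way repeated-measures ANOVAs will be conducted to observe the effects of the intervention on fasting insulin levels, shoulder ROM and function". It names neither an arm factor nor an affected-arm analysis.

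**The concern.** The movement loss that Phase 1 aims to reverse follows surgery, and surgery is on one side. The Background attributes it to damage to muscles and fasciae that depends on the operation. Averaging in a shoulder that was not operated on adds a measurement that may carry little or none of the effect. The reported group difference in degrees shrinks, the comparison usually loses power, and a deficit on the operated side can be hidden by a normal opposite arm.

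Shoulder function is named in the secondary objective, and the abstract lists shoulder ROM and strength first among the secondary outcomes. This is also not a detail left to a fuller document: the article does state how the ROM value is formed, and the rule it states is a poor one for this population.

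**Working it through.** **Reading the two sentences side by side.** The strength sentence says the measurements are made twice; the ROM sentence does not. For strength, the average can be over trials, over arms or over both. For ROM, only the arms are available to average over. Nothing in the statistical section overrides this.

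**Plan's own figure.** None exists for a shoulder outcome. The Sample size section gives 80 participants before dropout, based on insulin. With 1:1 allocation that is 80/2 = 40 per group, used below only to set a scale.

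**Inputs that must be assumed.** The article gives no shoulder SD, between-arm correlation or expected shoulder effect. Let

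- Δ = effect in the affected arm, and σ its SD;
- k = fraction of Δ that also appears in the unaffected arm;
- q = SD of the unaffected arm divided by σ;
- ρ = correlation between arms.

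**Effect in degrees.** The mean of the two arms carries (Δ + kΔ)/2 = Δ(1+k)/2. The ratio to the affected-arm effect is 0.50 at k = 0, 0.75 at k = 0.5 and 1 at k = 1. For illustration, 20 degrees confined to the operated side becomes 10. This does not depend on q or ρ.

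**Standardised effect.** The SD of the mean is σ√(1 + q² + 2ρq)/2, so the standardised effect is multiplied by (1+k)/√(1 + q² + 2ρq). With k = 0 and q = 1:

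- ρ = 0: 1/√2 = 0.71
- ρ = 0.5: 1/√3 = 0.58
- ρ = 0.8: 1/√3.6 = 0.53

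**Power.** Take an affected-arm effect of d = 0.634, which gives 80% power at 40 per group (two-sided 5%, noncentral t). Multiply d by the factor above with k = 0 and recompute:

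| Unaffected/affected SD ratio q | ρ = 0 | ρ = 0.5 | ρ = 0.8 |
|---|---|---|---|
| 1 | 51% | 37% | 31% |
| 0.5 | 71% | 56% | 50% |
| 0.25 | 78% | 69% | 64% |
| 0.1 | 80% | 76% | 74% |

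The top row is the harshest case. If the unaffected shoulder hardly changes, so that its change scores vary little, the effect and the SD shrink together and most of the power remains. The effect in degrees is still halved.

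**If both arms gain equally** (k = 1, q = 1), there is no dilution in degrees, and power rises to 98%, 90% and 84% at ρ = 0, 0.5 and 0.8. The argument therefore depends on the effect lying mainly on the operated side.

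**The case against.** The strongest reply is that this is loose wording in a condensed article. The ROM sentence may be the strength sentence with the number of trials left out, meaning an average of readings within each arm. The Discussion speaks of the two arms separately. Phase 2 adds tailored exercises for participants whose ROM or strength has not fully recovered, which would be hard to judge from a pooled value. This may well be the intention, but it is not what the ROM sentence says, and the same correction would be needed to say it.

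The second reply concerns strength, and it stands. A reader might infer that strength is halved in pounds too. The documents do not support that, for two reasons. First, the two trials give the average a natural meaning within each arm. Second, the Discussion reports "reduced shoulder strength in both the affected and unaffected arms due to lack of utilization", so a strength effect confined to the operated arm is not the article's own premise. The Discussion makes no such statement for ROM; there it says only that recovery varies with the type of operation.

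Third, a reader might take a fall to 31% power as the expected loss. It is one corner of an assumed grid, and milder assumptions leave nearly all of the 80%.

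Finally, these are secondary outcomes, and any pooling applies alike to both groups. It would dilute a difference, not favour exercise. That limits the consequence and does not remove it.

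**Conclusion.** The point holds for ROM. Read as written, the endpoint is the mean of an operated and an unoperated shoulder. An effect confined to the operated side is halved exactly in degrees; with partial gain in the other arm the ratio is (1+k)/2. The power cost is uncertain: for an effect confined to the operated side, 80% falls to somewhere between 31% and nearly 80%, depending on SDs and a correlation that the article does not give.

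For strength the finding is an ambiguity to resolve, with no claim of dilution. The primary insulin analysis and the sample size are untouched. The change should be made, but the trial does not depend on it.

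**What to change.** In Shoulder ROM, replace the averaging sentence with one such as: *The affected arm is the ROM endpoint. Repeat readings, where taken, are averaged within an arm. The unaffected arm is reported separately or as the affected-minus-unaffected difference.*

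In Shoulder strength, state that the two trials are averaged within each arm and that the arms are reported separately.

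The cost is a small rewording in each of two sections. Both arms are already measured at every visit where shoulder function is assessed, so no new data are needed. Fixing the rule before analysis also removes a later choice between affected arm, two-arm mean and difference.

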#### Shoulder strength

[The evaluation schedule: at baseline, 1 month from the baselines (± 2 weeks), 6 months from the baseline (± 1 month), and 12 months (± 1 month)]. Shoulder strength will be measured using a handheld dynamometer (j-tech Medical Industries Inc., UT, USA) in pounds (lb). The strength of peak muscle force will be measured using maximal voluntary isometric contraction (MVIC) in flexion, abduction, and extension [37]. All muscular strength measurements will be performed twice with both the affected and unaffected arms, and the average values will be used for the analysis.

### QOL (QOL)

[The evaluation schedule: at baseline, 1 month from the baselines (± 2 weeks), 6 months from the baseline (± 1 month), and 12 months (± 1 month)]. QOL will be measured using the EuroQOL-5 dimensions-5 levels (EQ-5D-5 L) descriptive system. Health-related QOL is divided into five dimensions (mobility, self-care, usual activities, pain/discomfort, and anxiety/depression), and there are five levels of response for each question (no problems, slight problems, moderate problems, severe problems, and extreme problems). Additionally, the EQ-5D-5 L assesses overall health status using a visual analog scale (EQ-VAS), a 100-mm scale with a score ranging from 0 (the worst health you can imagine) to 100 (the best health you can imagine). The Korean version of EQ-5D-5 L that will be used in this study was validated in a previous study [38].

#### Shoulder pain and disability index (SPADI)

[The evaluation schedule: at baseline, 1 month from the baselines (± 2 weeks), 6 months from the baseline (± 1 month), and 12 months (± 1 month)]. The shoulder pain and disability index (SPADI) is a self-administered questionnaire for shoulder pain with a total of 13 questions (five questions assessing shoulder pain and eight questions assessing disability). The reliability and validity of the Korean SPADI have been verified in a previous study (Seo, Lee, Jung, & Chung, 2012). Pain-free or most comfortable state scores 0, and painful or most uncomfortable state scores 10 for each SPADI item. Response scores within each subscale are summed, and a score out of 100 is given.

#### Anthropometric parameters and physical activity (PA)

[The evaluation schedule: at baseline, 1 month from the baselines (± 2 weeks), 6 months from the baseline (± 1 month), and 12 months (± 1 month)]. Body composition and Body mass index will be measured using InBody (BIO-SPACE®, InBody 720, Korea). The PA of participants will be measured using the Global Physical Activity Questionnaire (GPAQ), developed by the World Health Organization (WHO). It asks for any PA (including exercise) performed for at least 10 min during a typical week. Respondents will also report the time spent in PA performed at the workplace, transport, recreation, and sedentary behavior. The reliability and validity of the Korean GPAQ were examined in a previous study [39]. We will calculate PA as metabolic equivalent (METs) based on the GPAQ. Surgical complications that occurred within 30 days after surgery will be monitored through chart review. Surgical complications include surgical infection, wound complications (e.g., hematoma, wound dehiscence), seroma, and reoperation after breast cancer surgery.

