#### Sample size

The calculation for sample size was based on a previous study that evaluated the effects of 16 week mixed strength and endurance exercise on insulin levels in patients with breast cancer [31]. Based on a power of 80%, two-sided statistical significance level of 5%, and medium-sized effect size, the minimum required sample size would be 80 participants. Considering the dropout rate to be 20%, 96 patients with breast cancer are needed for the current study.

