## Randomization

Eligible participants will be randomly assigned to the exercise or control group, considering age, surgery method, and neoadjuvant chemotherapy as potential confounders. Each group would be matched into pairs such that the average age, surgical method, and neoadjuvant chemotherapy percentage are approximately equal (1:1 ratio). The exercise group will be provided with a systematic exercise program from post-operative day (POD) 1 to 12 months after surgery. The control group will receive the same preoperative and post-operative medical care and treatment as the exercise group (i.e., the usual care group thereafter), except for post-operative exercise. To evaluate the effects of the exercise intervention, measurements will be conducted five times for all the participants. The registration number of the Korean Clinical Trials Registry is KCT0007853. Data will be de-identified for analysis, and only study leaders at the university hospital will have access to identifiable information for all participants.

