### Intervention

#### Usual care group

Participants in the usual care group will be instructed to continue their routine activities. Twelve months after surgery, the usual care group will receive exercise counseling, exercise education, and an exercise diary, based on the measurement results.

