#### Exercise group

The exercise group will receive the usual care and exercise programs based on previously used exercise programs in clinical trials (KCT0006997). The exercise program according to the phases of cancer trajectory will consist of supervised and home-based exercises. Up to 1 month after surgery, weekly supervised exercises and daily home-based exercises will be provided. Thereafter, supervised exercise will be provided once per month, along with home-based exercise. The purpose of the supervised exercise session was to educate participants, enabling them to perform exercise daily at home with the help of exercise videos that included detailed instructions on how to perform each exercise. The exercise programs will be tailored based on the patient’s condition and each time point after surgery [1 month from the baseline (± 2 weeks); Phase 1, 6 months from the baseline (± 1 month); Phase 2, 12 months from baseline (± 1 month); Phase 3] (Fig. 2).

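### Thirty-day surgical complications come from chart review and are compared between arms, but only the exercise arm has weekly supervised contact in that month, so minor events may be recorded more often there

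*Protocol article*

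**What the plan says.** The section on anthropometric parameters and physical activity gives the source and the window: "Surgical complications that occurred within 30 days after surgery will be monitored through chart review". It also gives the list of events: "Surgical complications include surgical infection, wound complications (e.g., hematoma, wound dehiscence), seroma, and reoperation after breast cancer surgery". The section on statistical analysis methods makes these events a between-arm outcome: "Analysis of covariance (ANCOVA) will be applied to test the effect of an exercise intervention on body composition, PA, and complications".

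The intervention sections describe study contact in the first month. For the exercise group: "Up to 1 month after surgery, weekly supervised exercises and daily home-based exercises will be provided". For usual care: "Participants in the usual care group will be instructed to continue their routine activities". The randomization section adds that "The control group will receive the same preoperative and post-operative medical care and treatment as the exercise group", with post-operative exercise as the only exception. The same section says that "measurements will be conducted five times for all the participants". Table 1 places these measurements before surgery, on post-operative day 1, and at about 1, 6 and 12 months from baseline.

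**The concern.** The outcome window and the period of weekly sessions are almost the same month. Some listed events, such as reoperation, come to light whoever is watching. Others, such as a small seroma or a minor wound problem, reach the chart only if someone notices them and writes them down. One arm has about four or five more occasions in that month on which a problem could be noticed. Phase 1 exercises are tailored to the condition of the shoulder joint, so those contacts concern the operated region. The trial recruits from a single hospital, so a problem seen at a session could readily reach the surgical team.

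If that happens, the chance that an event is recorded depends on the arm. A raw count from the chart could then show an excess in the exercise arm with no true difference, or could hide a true reduction. The programme starts on post-operative day 1, so readers will look to this comparison for reassurance. Unless the route of detection is recorded at the time, the two explanations will be hard to separate afterwards.

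**Working it through.** **Step 1: contact in the 30-day window, side by side.**

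| | Exercise | Usual care |
|---|---|---|
| Routine surgical care | Same | Same |
| Study visit on post-operative day 1 | Yes | Yes |
| Study visit at 1 month ± 2 weeks from baseline | Yes | Yes |
| Weekly supervised sessions | Yes, about 4–5 | None described |

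The shared study visits do not remove the imbalance. Post-operative day 1 is too early for most of these events. The next visit is counted from the pre-surgery baseline. Taking a month as 30 days, it falls between about day 16 and day 44 (30 ± 14), so it may come after the 30-day window has closed. Table 1 shows no complication check at that visit.

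**Step 2: what must be true for bias to arise.** The source is the chart, so sessions matter only if they add chart entries or prompt extra clinic contact. The article does not say that they do and does not exclude it.

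**Step 3: size, by illustration.** The article gives no complication rate and no detection probability, so there is no stated figure to reproduce. Let p be the true rate of minor events in both arms, and let d_E and d_C be the proportions reaching the chart in the exercise and usual care arms. Then:

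- apparent difference = p × (d_E − d_C)
- apparent risk ratio = d_E / d_C
- extra events = 48 × apparent difference, where 48 = 96/2 because 96 patients are allocated 1:1

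Assumptions: p = 20–30%, d_E = 90%, d_C = 60–90%.

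| p | d_C | Charted, exercise v usual care | Difference | Risk ratio | Extra events in 48 |
|---|---|---|---|---|---|
| 20% | 90% | 18% v 18% | 0 points | 1.00 | 0 |
| 20% | 80% | 18% v 16% | 2 points | 1.13 | 1.0 |
| 30% | 80% | 27% v 24% | 3 points | 1.13 | 1.4 |
| 20% | 60% | 18% v 12% | 6 points | 1.50 | 2.9 |
| 30% | 60% | 27% v 18% | 9 points | 1.50 | 4.3 |

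**Step 4: chance of a false positive.** At 27% v 18%, the standard error is √[(0.27 × 0.73 + 0.18 × 0.82)/48] = 0.085. The bias is then 0.09/0.085 ≈ 1.06 standard errors, and the chance of p < 0.05 with no true difference is about 19%. At 18% v 16%, the standard error is 0.077, the bias is about 0.26 standard errors and the chance is about 6%. Both figures use the normal approximation, before the planned Bonferroni correction.

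**Step 5: wider assumptions.** Take full detection in the exercise arm and true rates of 10–40%. Relative detection of 0.7 in usual care gives a risk ratio of 1.43, 1.4 to 5.8 extra events, and a false-positive chance of 8–23%. Relative detection of 0.5 gives 2.0, 2.4 to 9.6 events, and 15–57%. Relative detection of 1.0 gives no bias. The result depends almost entirely on a quantity that the article does not supply.

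**The case against.** The strongest objection is that the mechanism is not in the document. The stated purpose of the supervised sessions is to teach patients to exercise at home with videos. Nothing says that exercise specialists inspect wounds, refer patients or write in the hospital chart. The chart records medical care, and that care is stated to be equal. A reader might infer that staff will handle the shoulder and refer any swelling, so that events will be found more often in the exercise arm. The document does not support that certainty, and this objection stands: only a possibility can be claimed. The equal-care statement does not settle the matter, however, because it excepts post-operative exercise, which is where the additional contact lies.

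A second objection concerns the outcome's weight. Complications are absent from the abstract's secondary outcomes, the secondary objective and Table 1. This also stands, and it limits the importance of the point. But the analysis section does name them for a test of the intervention effect. A reader might also take this to be the trial's only safety comparison. A condensed article cannot show that, since other adverse-event collection may be in the full protocol.

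A third objection is that 48 per arm gives little precision on complication rates in any case. That is true and the fix does not change it. Low precision is not a reason to leave a directional error in place.

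**Conclusion.** The point holds as a risk of unequal ascertainment, not as a demonstrated bias. The article fixes the source, the window, the event list and the between-arm test, and it gives weekly contact in that window to one arm only. Any resulting error would probably count against exercise, and would fall on minor events that depend on being noticed.

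Under the stated assumptions the apparent excess is 0 to 9 percentage points (0 to about 4 events in 48). Zero belongs in that range, because the sessions may add nothing to the chart. The rates and detection proportions are assumptions, not figures from the trial. The fasting insulin comparison is not affected. The change is worth making because it is cheap and the route of detection is difficult to reconstruct later.

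**What to change.** Amend the complications text in the section on anthropometric parameters and physical activity, and the matching sentence in the statistical methods:

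1. Report all charted 30-day complications in both arms as safety data.
2. For each event, record how it was first detected, and whether it was documented at a routine post-operative surgical visit scheduled alike in both arms. Name the visits that count.
3. Base the between-arm comparison, or at least a pre-specified sensitivity analysis, on events documented at those common visits, whoever first noticed them.
4. Extract the events without knowledge of allocation.

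Two apparent safeguards should be avoided. Restricting the count to events that led to treatment does not help, because a finding at a session can itself prompt treatment. Removing events first noticed at sessions would take true events out of the exercise arm only, including some that a routine visit would have found later, and would tilt the comparison in favour of exercise.

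The cost is one extra data field and a tighter definition, with no new visits and no change to care. Events seen only between routine visits leave the common-visit analysis but stay in the safety report. The common-visit rule reduces the imbalance and may not remove it, since a surgeon may already have been alerted by a session. The detection field shows how often that happened.
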